#### Evaluations throughout study participation

Evaluations performed throughout study participation will include physiological variables including respiratory and ventilation parameters (respiratory rate, SpO_2_, oxygen flow and/or FiO_2_), blood gases and chest x-ray (the worst values will be recorded). Results of investigations, ICU-acquired infections and data on oxygenation tolerance and efficacy as well as on comfort will be also collected.

ICU-acquired infections are defined as any new-onset infection starting more than 48 h after ICU admission for which the clinical team started a new antibiotic regimen. Every single infection diagnosis will be made using Centers for Disease Control and Prevention definitions [69].

#### Evaluation at the end of study participation

Evaluations performed at the end of study participation will consist of mortality on day 28, need for intubation, ICU and hospital lengths of stay and ICU-acquired infections. All elements allowing to record secondary endpoints will be collected.

#### Coordination and implementation of the trial

Each medical and paramedical team in the 31 participating ICUs were trained in the protocol and data collection using an electronic case-record form during formal meetings prior to screening and inclusion. The electronic case-record form was developed with CleanWEBTM, a centralized, secure, interactive, web-response system accessible from each study center, provided and managed by Telemedicine Technologies.

Local physicians and clinical research assistants in each participating ICU are responsible for daily screening and inclusion of patients, compliance with protocol, availability of data requested for the trial and completion of the electronic case-record form. In accordance with French law, the electronic case-record form and database were validated by the appropriate committees (Comité Consultatif sur le Traitement de l’Information en matière de Recherche dans le domaine de la Santé; Commission Nationale de l’Informatique et des Libertés).

#### Interim analysis

One interim analysis by an independent Data Safety and Monitoring Board is planned after the occurrence of 100 deaths. The Data Safety and Monitoring Board will be blinded to allocation of groups and may decide premature termination of the study. The board consists of one methodologist, one pulmonologist, and one intensivist. Data are blindly analyzed but unblinding is possible on request of the Data Safety and Monitoring Board. An extraordinary meeting may be requested by the principal investigator or the methodologist, in the case of unexpected events that might affect continuation of the protocol.

### Blinding

Given the nature of the interventions, physicians, nurses, and patients cannot be blinded for the randomized interventions. The analysis will be blinded to allocation of groups.

### Study outcomes

#### Primary endpoint

The primary endpoint of this trial is day-28 mortality.

#### Secondary endpoints

The secondary endpoints are: intubation rate (proportion of patients requiring invasive mechanical ventilation) on day 28, patient comfort VAS, dyspnea (VAS and Borg scale), respiratory rate, oxygenation (based on the lowest SpO_2_ value and on PaO_2_/FiO_2_ from day 1 to day 3, ICU stay length, incidence of ICU-acquired infections.

### Statistical methods

All statistical analyses will be performed using SAS (SAS Inc., Cary, NC, USA) and R (http://www.R-project.org/) software.

#### Sample size calculation

Based on a 30% day-28 mortality rate in usual-care oxygen group, and a 20% day-28 mortality rate in the HFNO group, with α set at 5%, to obtain a 90% power for demonstrating superiority for the primary outcome, we need 778 patients (389 in each group).

Recruitment is expected to take 30 months, and 28 additional days will be required for follow-up.

#### Interim analyses

One interim analysis will be performed once 100 deaths will have been observed. Due to inflation of type I error consideration, it will use the Haybittle-Peto boundary, that is a *p* value threshold of 0.001 for the interim analysis (while the terminal analysis will use a threshold of 0.05, as scheduled in the sample size computation). Moreover, to get insight in the difference across arms in terms of futility or efficacy, the Bayesian posterior probability of the 28-day mortality rate and of the log odds ratio will be computed, using a uniform non-informative prior. The final analysis will be started after inclusion of the planned number of patients.

#### Methodology of the statistical analysis

The main comparison based on the intention-to-treat principle will compare the intervention arm to the control arm on the full-set of randomized patients. The primary hypothesis is superiority of the NIV in terms of 28-day mortality (primary outcome). For all secondary outcomes, our hypothesis is that HFNO is superior over standard oxygen, with two-sided *p* values for comparison tests. Secondary and exploratory comparisons of the primary endpoint will look for treatment-by-covariate interactions according to the subsets defined above. Finally, a per-protocol analysis will be performed.

#### Missing values and outliers

Missing values for the main outcome measure are not expected to be observed; nevertheless, in case of occurrence, they will be handled using time-to-event methods in which each patient contributes to the estimate of failure time distribution until they are lost-to-follow up or withdrawn from the study using competing-risks estimates. Missing values for predictors will be imputed using multiple imputation techniques.

#### Analysis of the primary outcome

The main endpoint is binary, as all patients will be followed until day 28, at which time they will be classified as alive or dead. The relative risk of hospital death in the experimental vs. the control arm will be estimated to assess the effectiveness of the intervention, with 95% confidence interval. Analyses adjusted on potential confounders will be performed. Intervention-by-subsets interactions will be tested using Gail and Simon statistics. In case of significant interaction, subset analyses will be performed on each subset.

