## Methods/design

### Design and settings

The HIGH trial is a prospective, multicenter, open-label RCT comparing HFNO vs. other oxygenation strategies (low/medium-flow oxygen) in immunocompromised patients requiring oxygen. The study hypothesis is that early HFNO decreases mortality on day 28 after randomization in immunocompromised patients requiring ICU admission for ARF. Figure 1 shows an adapted version of the SPIRIT Figure for the trial (Additional file 1).

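### The primary analysis section defines its effect estimate on hospital death, although the primary endpoint, the hypothesis and the sample size all concern death by day 28

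*Protocol article*

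**What the plan says.** The protocol article states the primary outcome consistently in almost every place:

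- Primary endpoint: "The primary endpoint of this trial is day-28 mortality".
- Design and settings: "The study hypothesis is that early HFNO decreases mortality on day 28 after randomization".
- Sample size calculation: "Based on a 30% day-28 mortality rate in usual-care oxygen group, and a 20% day-28 mortality rate in the HFNO group".
- Methodology of the statistical analysis: superiority is claimed "in terms of 28-day mortality (primary outcome"). That sentence names NIV as the treatment, which is a separate error and does not bear on this point.

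The Abstract, the Interim analyses section and the section on evaluation at the end of study participation use the same 28-day horizon. The Background gives its complement, survival at day 28.

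The section Analysis of the primary outcome opens in line with this: the endpoint is binary, with vital status determined at day 28. The next sentence sets the effect measure, with a 95% confidence interval, on a different outcome: "The relative risk of hospital death in the experimental vs. the control arm will be estimated to assess the effectiveness of the intervention".

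**The concern.** Consecutive sentences of one paragraph name two different outcomes. The second is the only place where the article says which quantity will be estimated to judge the intervention, so it governs the headline result.

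Hospital death is not another name for death by day 28. It depends on where the patient dies and on when the patient leaves hospital, and it carries no fixed horizon. Read literally, the sentence would have the trial report an outcome that it neither declared nor sized for. Left as it stands, it also gives a pre-specified primary estimate two possible readings in an open-label trial, where the choice between two mortality estimates should not be open once results are known.

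**Working it through.** **1. What the sample size belongs to.** Inputs from the Sample size calculation section: control rate 0.30 ("Based on a 30% day-28 mortality rate in usual-care oxygen group"), experimental rate 0.20 ("a 20% day-28 mortality rate in the HFNO group"), and the error rates ("with α set at 5%, to obtain a 90% power for demonstrating superiority for the primary outcome"). Allocation is 1:1 (Randomization section). Sidedness is not stated for the primary test; two-sided is the reading that reproduces the figure.

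Unpooled normal approximation, per arm:

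n = (z₀.₉₇₅ + z₀.₉₀)² × [p₁(1 − p₁) + p₂(1 − p₂)] / (p₁ − p₂)²

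= (1.960 + 1.282)² × (0.21 + 0.16) / 0.10²

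= 10.51 × 0.37 / 0.01 ≈ 388.8, rounded up to 389, hence 2 × 389 = 778.

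This matches the plan exactly. The pooled-variance formula gives 392 per arm, and 389 per arm has 89.8% power under it. A one-sided 5% test would need only 320. The design relative risk is 0.20 / 0.30 = 0.667. All of these figures are for death by day 28.

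**2. How hospital death relates to death by day 28.** As sets of patients:

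hospital deaths = deaths by day 28 − deaths by day 28 after hospital discharge + in-hospital deaths after day 28.

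The two outcomes coincide only if both correction terms are zero or happen to cancel. There are two literal readings of the sentence:

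- *Death in hospital, within 28 days.* The last term drops out. The estimate then misses every death that follows discharge but precedes day 28.
- *Death in hospital, without a time limit.* Both terms apply. The article, however, plans 28 additional days of follow-up after recruitment and says that patients are followed to day 28, so late in-hospital deaths lie outside the follow-up it describes.

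Neither reading gives the declared endpoint.

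**3. Whether hospital death is supported elsewhere as a trial outcome.**

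| Section | Outcome named |
|---|---|
| Abstract | Day-28 mortality |
| Design and settings | Mortality at day 28 after randomization |
| Evaluation at the end of study participation | Mortality at day 28; hospital mortality absent (hospital length of stay is recorded) |
| Primary endpoint | Day-28 mortality |
| Secondary endpoints | Hospital mortality absent |
| Sample size calculation | Day-28 mortality |
| Interim analyses | 28-day mortality rate |
| Methodology of the statistical analysis | 28-day mortality |
| Analysis of the primary outcome, first sentence | Vital status at day 28 |
| Analysis of the primary outcome, second sentence | Hospital death |

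The only other mention of hospital mortality is in the Background, for an earlier uncontrolled series of 45 patients with hematological malignancies. That series supplies no rates for the two arms of this trial.

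**The case against.** The strongest reply is that the documents already settle the question. The section is headed as the analysis of the primary outcome, its first sentence fixes vital status at day 28, and every other statement of the outcome agrees. One stray word against so many statements is most naturally a drafting slip, and an analyst would probably compute the relative risk of the binary variable just described. This stands as far as intent goes: the endpoint itself is not in doubt. It does not remove the defect, because the slip sits in the sentence that specifies the primary estimate rather than in background text. A detail left to a fuller plan would be no finding; this is something that the article states, and states wrongly.

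Two stronger readings are tempting, and the documents support neither.

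- *A reader might infer a loss of power.* The article gives no hospital mortality rates by arm, and assumed rates move power either way. At 389 per arm (pooled variance, two-sided 5%), higher rates of 35% v 25% give 86.2%, but 35% v 23.33% gives 94.9%. Lower rates of 28% v 18% give 91.4%, but 25% v 16.67% gives 81.7%. Scenarios that simply shrink the difference between arms show only that smaller effects are harder to detect; nothing links them to the wording. No power figure for hospital death should be reported.
- *A reader might infer bias from different discharge rules in the two arms.* Both intervention sections tie ICU discharge to the same saturation and oxygen-flow condition. The further items in the HFNO section are criteria for stopping HFNO. Neither section states a rule for hospital discharge, which is what hospital death would depend on. Differential bias is not shown.

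**Conclusion.** The point holds as an internal contradiction in the definition of the primary estimate. The section classifies patients at day 28 and then estimates the relative risk of an undefined outcome that is neither a listed endpoint nor part of the end-of-study evaluation. Followed literally, it yields the wrong primary estimate and confidence interval.

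Its size cannot be put in numbers. How far the two outcomes would differ depends on deaths after discharge and on in-hospital deaths after day 28, and the documents give neither. What can be said is that the stated 90% power belongs to day-28 mortality and does not carry over to hospital death in either direction. The sample size is correct as planned, given a two-sided test. A wording slip is the most likely explanation, and the contradiction should be removed before the final analysis.

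**What to change.** In Analysis of the primary outcome, replace the relative risk of hospital death with the relative risk of death from any cause by day 28 after randomization. State that the primary conclusion and its 95% confidence interval rest on that quantity, and carry the same wording into the analysis plan. If hospital mortality is of interest, define it, including its time horizon, and list it as a secondary outcome.

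The cost is one sentence. Mortality at day 28 is already part of the end-of-study evaluation, so the primary estimate needs no new data. The 389 per arm, the 778 overall and the design relative risk of 0.667 stay as they are.

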#### Analysis of the secondary outcomes

Competing-risk endpoints (ICU-acquired events including intubation, ICU-acquired infection) will be analyzed using competing-risk methods. Specifically, cumulative incidences of the event of interest will be estimated, taking into account the competition between death or discharge alive from the ICU and the event of interest, then compared using the Gray test. Adjustment for potential confounders will be based on cause-specific Cox models. ICU length of stay will be analyzed overall and in survivors and dead patients, separately. The former analysis will be based on Kaplan-Meier estimates while the later on the competing-risk estimator, as described above. Analyses of longitudinal outcomes (oxygenation, dyspnea, patient’s comfort) will be based on joint models, taking into account the right censoring of the data.

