### Randomization

Randomization will be stratified on three factors, measured at study inclusion, namely: (1) time since ICU admission, segregating day 0 (calendar date of ICU admission), day 1, day 2 vs. ≥ day 3; (2) hypoxemia severity, segregating oxygen flow < vs. ≥ 9 L to reach SpO_2_ ≥ 95% at randomization, and (3) shock, based on the administration of catecholamine. Thus, analysis could consider treatment-by-subset interaction on such strata.

Randomization will be achieved using an electronic system incorporated in the eCRF and R software (http://www.R-project.org/). The impact of the intervention will be assessed at the patient level. The randomization unit is the center. Randomization will be centralized on a web site to ensure allocation concealment at the trial statistical center. Patients will be randomized into two parallel groups in a 1:1 ratio. Randomization will be stratified (see above), resulting in eight different randomization lists that will be pre-specified and balanced through the use of permutation blocks of fixed size that will not be disclosed to the local investigators, to ensure allocation concealment and to avoid all risk of bias in patient selection.

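### As worded, ICU stay is analysed separately in survivors and in the dead, groups formed by the primary outcome; the text should specify cumulative incidences in all randomized patients

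*Protocol article*

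**What the plan says.** The section Analysis of the secondary outcomes says that "ICU length of stay will be analyzed overall and in survivors and dead patients, separately". The next sentence assigns the estimators: "The former analysis will be based on Kaplan-Meier estimates while the later on the competing-risk estimator, as described above". The method described above it is a cumulative incidence in which death and live discharge from the ICU are competing events, with arms compared by the Gray test.

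The section Methodology of the statistical analysis says, for all secondary outcomes, that "our hypothesis is that HFNO is superior over standard oxygen", and plans two-sided tests. ICU stay is a listed secondary endpoint. Nothing marks the separate analyses as descriptive.

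The primary endpoint is day-28 mortality. Under Sample size calculation, the trial is sized for a fall from 30% in the control group to "a 20% day-28 mortality rate in the HFNO group".

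The text does not say whether vital status for the separate analyses is taken at ICU exit or at day 28. It also does not say whether those analyses are restricted to each group or run in all randomized patients.

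**The concern.** Survival is determined after randomization, and the trial is designed on the expectation that treatment changes it. If it does, survivors in the two arms are different kinds of patient. The HFNO survivors include people who would have died on standard oxygen, and the control survivors do not. The same holds in reverse among the dead: control deaths include patients whom HFNO would have saved, and HFNO deaths do not.

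A between-arm test within either group is therefore not protected by randomization, least of all when HFNO works. It could yield a significant difference in ICU stay that reflects only who is in each group.

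The estimator does not help. Among survivors no death competes with discharge, so a cumulative incidence is simply one minus Kaplan-Meier. Among the dead, if status is taken at ICU exit, death is the only exit. If status is taken at day 28, some of the dead may have left the ICU alive first, but the selection remains. So the sentence either specifies a biased comparison or misdescribes one made in all randomized patients.

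**Working it through.** **Inputs from the protocol article.** Day-28 mortality 30% (control) and 20% (HFNO), α 5%, power 90%, 389 per group, 1:1 allocation.

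**Reproducing the sample size.** Two-sided test, unpooled variance: n = (1.960 + 1.282)² × (0.30×0.70 + 0.20×0.80) / 0.10² = 388.8, so 389 per group. This matches the plan, and the 30% and 20% rates are used below.

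**Who is in each group.** Assume HFNO harms no one. Then 70% survive in either arm (always-survivors), 10% survive only on HFNO (saved patients), and 20% die in either arm.

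- Survivors: 389 × 0.70 = 272 (control), 389 × 0.80 = 311 (HFNO)
- Deaths: 389 × 0.30 = 117 (control), 389 × 0.20 = 78 (HFNO)
- Saved patients as a share of HFNO survivors: 0.10 / 0.80 = 12.5%
- Patients whom HFNO would have saved, as a share of control deaths: 0.10 / 0.30 = 33%

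**Size and direction in survivors.** With no effect on any always-survivor's stay, the spurious difference in mean stay (HFNO minus control) is 0.125 × (mean stay of saved patients − mean stay of always-survivors).

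The documents give no stay data. The table assumes an always-survivor mean of 7 days and lognormal stays with log SD 0.8. Rejection is for a two-sided 5% rank test in survivors, 389 per arm, 1,500 replicates. The last column is the HFNO-minus-control difference in the proportion of all randomized patients discharged alive from the ICU by day 28; for it, the mean time to death is assumed to be 8 days.

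| Mean stay of saved patients (days, assumed) | Spurious difference in survivors (days) | Rejection in survivors | Difference in discharge alive by day 28 |
|---|---|---|---|
| 4 | −0.4 | 17% | +0.10 |
| 7 | 0.0 | 5% | +0.10 |
| 10 | +0.4 | 9% | +0.10 |
| 14 | +0.9 | 22% | +0.09 |
| 21 | +1.75 | 43% | +0.08 |

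**Direction in the dead.** The corresponding difference is (1/3) × (mean time to death of those who die in either arm − that of the patients HFNO would have saved). With an assumed 6 days for the former, values of 3, 6, 10 and 14 days for the latter give +1.0, 0, −1.3 and −2.7 days. The sign again depends on the assumption.

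**A second model.** Each patient has a normal latent risk, and death occurs above its 70th percentile (control) or 80th (HFNO). Log stay in survivors has correlation r with that risk, and log time to death has correlation −r. The log SD is 0.8, the median parameters are 8 and 9 days, and HFNO has no effect on stay. The test is a two-sided 5% log-rank test within each group. Ranges are across repeated runs.

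| r (assumed) | False positives, survivors | False positives, dead |
|---|---|---|
| 0 | about 5% | 5–6% |
| 0.3 | 8–9% | 8–9% |
| 0.5 | 15–17% | 14–16% |
| 0.7 | 34–36% | 30–31% |

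For r = 0.3, 0.5 and 0.7, mean stay in HFNO survivors is about 4%, 7% and 10–11% longer, and in the HFNO dead about 5%, 9% and 13% shorter. These directions follow from the signs given to r. With r = −0.3 they reverse. Both models treat every death as a death in the ICU.

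**The case against.** The strongest reply is that the second sentence shows what was meant. Overall stay is time to leaving the ICU by any route, for which Kaplan-Meier is used. Stay by route of exit is then split by the competing-risk estimator. That estimator does useful work only if both exits are possible, which points to all randomized patients. On this reading the recommended analysis is already planned, and only the wording is loose. This stands as a plausible account of intent. It does not settle the matter, because the first sentence names groups of patients, not types of exit, and no analysis set is given.

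Two stronger readings are tempting, and the documents support neither. A reader might infer that a mortality benefit must make HFNO survivors appear to stay longer. That needs saved patients to stay longer than always-survivors, on which the documents are silent; equal stays give no bias and shorter stays reverse it. A reader might also infer that the plan definitely tests stay within each group and will report the results as treatment effects. The superiority hypothesis covers secondary outcomes in general, but the listed endpoint is ICU stay as such, with no separate endpoint for survivors or for the dead.

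It is also true that an overall analysis is planned and that this is one secondary endpoint in a condensed article. Those facts limit the consequence. They do not make the stated split valid, and the point concerns what the article says, not detail left to an analysis plan.

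**Conclusion.** The point holds as a defect of specification. One of the two readings of the sentence gives a comparison that randomization does not protect, and the text does not exclude it. On that reading, 12.5% of HFNO survivors lack a control counterpart at the design rates, assuming HFNO harms no one. The resulting false-positive rate runs from the nominal 5% to about 35% in survivors and about 30% in the dead over r = 0 to 0.7, and to 43% in survivors in the most extreme stay scenario tried. All these rates rest on assumed stay distributions, and the direction is not determined by anything in the documents. The consequence is confined to one secondary outcome; the primary analysis and the sample size are unaffected.

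**What to change.** Replace the wording on the separate analyses with this: in all randomized patients, counted from randomization, estimate the cumulative incidence of ICU discharge alive (ICU death competing) and of ICU death (discharge alive competing), and compare discharge alive between arms by the Gray test. Stay within survivors and within the dead may still be tabulated, as description only, with no p value and no superiority claim. State when vital status is taken for that table.

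The cost is one or two sentences and no new data. The familiar figure for stay in survivors loses its test. Discharge alive also reflects mortality as well as speed of discharge, so it should be read beside the ICU-death curve and not as a pure measure of stay. In the scenarios above, where HFNO improves mortality only, it favours HFNO throughout (+0.08 to +0.10 by day 28).
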